#### 8 and 16 mg tablets

| 8 mg tablets | 16 mg tablets |
|--------------|---------------|
| 2 tablets    | 1 tablet      |
| 3 times/day  | 3 times/day   |

#### 24 mg tablets

The dosage for adults is 48 mg divided over the day.

|               |
|---------------|
| 24 mg tablets |
| 1 tablet      |
| 2 times/day   |

The assignment of the patient to betahistine dihydrochloride is not decided in advance by this protocol but falls within current practice. The prescription of betahistine

[figure not shown]

dihydrochloride (Betaserc®) is clearly separated from the decision to include the patient in this program. No additional procedures (other than standard of care) shall be applied to the patients.

The patients must provide written consent to the Investigator to use and/or disclose personal and/or health data before entry into this program.

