#### **7.1.1 Inclusion Criteria**

1. Male or female with age  $\geq 18$  years.
2. Patients with vestibular vertigo of known or unknown origin, and for whom the physician has decided to prescribe 48 mg of betahistine dihydrochloride (Betaserc®) in accordance with locally approved label.
3. Patients who are willing and able to provide authorization to the investigator to use and/or disclose personal and/or health data.
4. Patients who started betahistine dihydrochloride (Betaserc®) therapy not more than 5 days prior to sign Patient Authorization (Consent) for Use/Disclosure of Data.

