#### **7.1.2 Exclusion Criteria**

1. Patients with any condition which, in the opinion of the Investigator, makes the patient unsuitable for inclusion based on clinical judgment.
2. Labeled contraindications of betahistine dihydrochloride (Betaserc®) treatment.
3. Patients with middle or inner ear infection.
4. Patient with psychiatric disorders, significant neurological disorder or spinal cord damage.

[figure not shown]

5. Patients receiving any other agents for peripheral vestibular vertigo such as diuretics, transtympanic gentamycin, cinnarizine, competitive antagonist of histamine, blocking H1-histamine receptors.
6. Patients undergoing ear surgery for vestibular disorders.
7. Female patients who are pregnant, planning to become pregnant or are breast-feeding.
8. Inability to comply with the protocol requirements.
9. Participation in any other clinical trial within last 30 days.
10. Patients who had previous betahistine therapy within 4 weeks of start of current betahistine dihydrochloride (Betaserc®) treatment course.

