## **7.2 Number of Patients to be Enrolled**

A total of 310 patients will be enrolled in this program from approximately 10-35 centers in Russia and Ukraine.

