### **7.5.2 Description of Activities**

#### **Visit 1, Baseline / Start of therapy:**

Following activities will be performed:

- Sign and Date of Patient Authorization (Consent) for Use/Disclosure of Data.
- Check inclusion/exclusion criteria
- Collect demographic data
- Register date of start of betahistine dihydrochloride (Betaserc®) treatment (can differ from enrollment date, please see section 7.1.1)
- Register concomitant medication

[figure not shown]

- Collect medical history
- Allocation of patient identification number
- Performed routine physical examination including vitals (heart rate, systolic and diastolic blood pressure)
- Collect specific underlying ICD-10 diagnosis account for Vestibular Vertigo
- Register of the number of vertigo attacks for the previous month
- Evaluate patient's clinical conditions based on SVVSLCRE
- SAE monitoring

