### Data Analysis Set

**All Patients Set** will include all patients who signed patient authorization form to participate in the study. This population will be used for presenting disposition of subjects.

**Full Analysis Set** will include those patients who attended Visit 1 and who were administered at least one dose of betahistine dihydrochloride (Betaserc®), as assessed in the CRF. This population will be used for the reporting of effectiveness results.

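### Enrolment may follow the first dose by up to 5 days, with no rule on whom to offer it and no count of those missed, so the primary response proportion may carry a selection bias of unknown size

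*Protocol*

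**What the plan says.** Section 7.1 leaves the choice of treatment to current practice and states that the prescription "is clearly separated from the decision to include the patient in this program".

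Section 7.1.1, criterion 4, admits "Patients who started betahistine dihydrochloride (Betaserc®) therapy not more than 5 days prior to sign Patient Authorization (Consent) for Use/Disclosure of Data". Section 7.5.2 has the start date of treatment registered at Visit 1 and notes that it "can differ from enrollment date, please see section 7.1.1".

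Section 7.1.2, criterion 1, is an open clause: it excludes anyone with a condition that, "in the opinion of the Investigator, makes the patient unsuitable for inclusion based on clinical judgment".

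Section 7.2 fixes only the total: "A total of 310 patients will be enrolled in this program from approximately 10-35 centers in Russia and Ukraine". Neither that section nor the rest of 7.1 says which eligible patients a centre must approach.

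In section 11.0 the widest analysis set, used for disposition, "will include all patients who signed patient authorization form to participate in the study". The Full Analysis Set, used for effectiveness, takes those who attended Visit 1 and received at least one dose. The program activities in Table 2 and the Visit 1 list contain no record of eligible starters who were not enrolled.

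**The concern.** The primary result is one proportion from a single arm, meant to describe effectiveness in routine outpatient care. Its value depends on who enters the sample. With no comparator, any selection on likely outcome passes straight into the estimate.

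Three features combine. The first days of treatment may already be known when enrolment is decided. Centres are free to choose whom to approach until 310 patients are reached. Accounting begins only at signature. A patient who stops, tolerates the drug badly or sees no benefit in those days, and who is not approached, leaves no trace. The report could then show neither that such patients existed nor how many there were. A later statistical analysis plan cannot repair this, because it cannot analyse data that were never collected.

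**Working it through.** **Inputs from the protocol (section 11.0, Sample size considerations).** Expected response 80%; two-sided 95% confidence interval by normal approximation; half-width 5.0 points; dropout about 20%.

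**The protocol's own figures.**
- n = 1.96² × 0.80 × 0.20 / 0.05² = 245.85, rounded up to 246, as stated. The half-width at 246 is 4.999 points.
- 246 / 0.80 = 307.5, rounded up to 308, as stated, and then set at 310.

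These figures are correct. They describe random error only. Selection at entry is a bias, so it does not change the sample size and is not covered by the 5-point half-width.

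**Bias formula.** Let f be the share of eligible starters never enrolled, and q the response they would have had. With 80% observed in those enrolled:

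- response in all starters = (1 − f) × 80 + f × q
- bias = 80 − response in all starters = f × (80 − q)

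The protocol gives neither f nor q. The values below are assumptions, chosen to show the range.

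| f | q = 20% | q = 30% | q = 40% | q = 80% |
|---|---|---|---|---|
| 5% | 3.0 points | 2.5 | 2.0 | 0 |
| 10% | 6.0 | 5.0 | 4.0 | 0 |
| 15% | 9.0 | 7.5 | 6.0 | 0 |

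**When the bias equals the planned half-width.** Setting f × (80 − q) = 5 gives f = 5/80 = 6.25% if none of those missed would have responded, and f = 5/40 = 12.5% if 40% would have.

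**A force in the other direction.** The same 5-day window allows the baseline score to be taken after treatment has begun, so improvement already made is not counted. Suppose g percentage points of the enrolled lose responder status in this way. With f = 5% and q = 0, response in all starters is 0.95 × 80 = 76%, the observed figure is 80 − g, and the net bias is 4 − g: +4 points at g = 0, +2 at g = 2, −1 at g = 5 and −6 at g = 10. Here too g is assumed.

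**The case against.** A reader might infer that early failures and early stoppers never enter the denominator and that response is therefore inflated. The protocol does not support this.

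- Five days is a ceiling, not a run-in. Visit 1 is labelled as baseline and start of therapy, and enrolment on the day of the first dose is allowed.
- No criterion excludes a patient who has not improved or has already stopped. The open clause in exclusion 1 concerns conditions that make a patient unsuitable, not poor response.
- Anyone who attends Visit 1 and has taken one dose is in the Full Analysis Set, and Visit 3 doubles as the early-termination visit. Only a starter who stops or does badly before consent and is not approached is lost.
- The direction is not demonstrated. Section 4.0 describes conditions whose acute phase resolves within several days, so someone who stops before consent may have recovered. The late baseline can also lower the measured response.

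Nor is the sentence that separates prescribing from inclusion a defect. It protects the non-interventional character of the program. That the same physician prescribes and enrols is a reasonable inference, but that sentence does not say so.

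A reader might add that exclusion 10, which bars "Patients who had previous betahistine therapy within 4 weeks of start of current betahistine dihydrochloride (Betaserc®) treatment course", lets in patients known to have done well on an earlier course. That is a question of prior exposure, not of early course, and a split by earlier use is a subgroup choice that can be left to the analysis plan.

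It can also be said that the missing rule is an omission, and that screening logs may sit in site documents not shown. That lowers the priority but does not answer the point. How the sample is formed belongs in section 7.1, and the protocol itself fixes the start of accounting at signature.

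**Conclusion.** The point holds in a limited form. Entry up to 5 days after the first dose, no duty to offer enrolment to every eligible starter and disposition counted only from authorisation together make selection on early course possible. The planned data could not size it. The effect on the primary proportion is plausibly upward but not shown to be so.

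The 2 to 9 points rest entirely on assumed values: 5 to 15% of starters missed, with 20 to 40% response among them against 80% in those enrolled. The upper value of 15% is high for a loss within 5 days; it is three quarters of the roughly 20% dropout that the protocol assumes for the program as a whole. If those missed would have responded like the rest, there is no bias. The net sign, allowing for the late baseline, is not fixed by the protocol. This is a cheap improvement, not an error in the sample size or the analysis.

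**What to change.** 1. In section 7.1, state that each centre offers enrolment to all consecutive patients who meet 7.1.1 and 7.1.2, from its opening until its last patient.
2. Keep an anonymous tally at each site of eligible patients prescribed 48 mg/day who were not enrolled, with the reason, including treatment stopped before consent. Report the enrolment fraction.
3. From the start date already registered at Visit 1, show the primary proportion by days from first dose to Visit 1 (0 versus 1 to 5). This does not isolate selection, because a late baseline also affects the second group, but it shows how many patients entered late and whether their result differs.

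The cost is one sentence in section 7.1, a short tally per site and one additional table, with slight extra paperwork for the centres. Treatment, visits and sample size are unchanged.

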#### **7.1.1 Inclusion Criteria**

1. Male or female with age  $\geq 18$  years.
2. Patients with vestibular vertigo of known or unknown origin, and for whom the physician has decided to prescribe 48 mg of betahistine dihydrochloride (Betaserc®) in accordance with locally approved label.
3. Patients who are willing and able to provide authorization to the investigator to use and/or disclose personal and/or health data.
4. Patients who started betahistine dihydrochloride (Betaserc®) therapy not more than 5 days prior to sign Patient Authorization (Consent) for Use/Disclosure of Data.

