### **6.3 Primary Endpoint**

1. Number and proportion of patients with clinical response at the end of observational treatment period that is determined based on the Scale for Vestibular Vertigo Severity Level and Clinical Response Evaluation (SVVSLCRE) (Figure 1 and Table 1) in the total program population.

The patients will evaluate vestibular vertigo severity at baseline and end of observational treatment period based on the SVVSLCRE.

[figure not shown]

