**Figure 1. Scale for Vestibular Vertigo Severity Level and Clinical Response Evaluation (SVVSLCRE).**

| Severity levels:   |   | Level I.
Absent or very mild vestibular vertigo
0 – 2   |   | Level II.
Mild vestibular vertigo
>2 – 4                                    |   | Level III.
Moderate vestibular vertigo
>4 – 6                                  |   | Level IV.
Severe vestibular vertigo
>6 – 8          |   | Level V.
Very severe vestibular vertigo
>8 – 10    |  |
|--------------------|---|---------------------------------------------------------------|---|-----------------------------------------------------------------------------------|---|--------------------------------------------------------------------------------------|---|-----------------------------------------------------------|---|----------------------------------------------------------|--|
|                    |   | Disturbances can be easy ignored. activities is not disrupted |   | Disturbances can be ignored with some efforts, activities can be slightly limited |   | Disturbances can be ignored with great efforts, activities can be moderately limited |   | Disturbances cannot be ignored, most activities disrupted |   | Disturbances cannot be ignored, all activities disrupted |  |
| 0                  | 1 | 2                                                             | 3 | 4                                                                                 | 5 | 6                                                                                    | 7 | 8                                                         | 9 | 10                                                       |  |
| Absent of symptoms |   | Very severe symptoms                                          |   |                                                                                   |   |                                                                                      |   |                                                           |   |                                                          |  |

[figure not shown]

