**Table 1. Clinical responses define as a following:**

| Change of patient's clinical conditions of vestibular vertigo | Shift direction based on the SVVSLCRE from Baseline to end of observational treatment period |
|----------------------------------------------------------------------|-----------------------------------------------------------------------------------------------------|
| Worsening                                                            | All other shifts                                                                                    |
| No change                                                            | V to V; IV to IV; III to III; I to I                                                                |
| Moderate                                                             | V to IV; IV to III; III to II; II to I                                                              |
| Good                                                                 | V to III; IV to II; III to I                                                                        |
| Very good                                                            | V to II; IV to I                                                                                    |
| Excellent                                                            | V to I                                                                                              |

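### Patients at baseline Level I can enter the primary denominator although Table 1 gives them no improving shift, and the protocol does not say which Table 1 rows count as response

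*Protocol*

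**What the plan says.** **Entry.** Section 7.1.1 asks for "Patients with vestibular vertigo of known or unknown origin, and for whom the physician has decided to prescribe 48 mg of betahistine dihydrochloride". The other three inclusion criteria concern age, data authorization and a treatment start no more than 5 days before authorization is signed. None of the ten exclusion criteria in 7.1.2 refers to severity.

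**Scale.** In section 6.3, Figure 1, Level I covers scores 0 to 2 and is labelled "Absent or very mild vestibular vertigo".

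**Response table.** Section 6.3, Table 1, classifies shifts from baseline to the end of observational treatment. The smallest improvement, Moderate, is "V to IV; IV to III; III to II; II to I". 'No change' is "V to V; IV to IV; III to III; I to I". 'Worsening' is "All other shifts". The table's heading presents all six rows as clinical responses.

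**Primary endpoint.** Section 6.3 defines it as "Number and proportion of patients with clinical response at the end of observational treatment period that is determined based on the Scale" (the SVVSLCRE), taken in the whole program population. Neither 6.3 nor the primary analysis in section 11.0 names the rows that make a patient a responder.

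**Denominator.** The Full Analysis Set in section 11.0 requires attendance at Visit 1 and one dose. Of this set it says "This population will be used for the reporting of effectiveness results". It carries no condition on baseline severity.

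**The concern.** The entry criteria, the analysis set and the response table do not fit together. Patients may start at the lowest level of the scale, and Table 1 allows for this by listing I to I. Such a patient has nowhere lower to go, yet stays in the denominator of the only primary endpoint.

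Two features of the protocol make a Level I baseline possible:

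- Treatment may begin up to 5 days before consent, so the Visit 1 score can be an on-treatment score.
- The Introduction describes peripheral vertigo as episodic or persistent, and Figure 1 states no recall period, so a patient seen between attacks could score low.

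What is at stake is how the primary proportion is read. It would depend partly on how many near-asymptomatic patients the sites enrol. With response undefined, even the direction of that dependence is open. Enrolling more patients narrows the interval but does not remove the effect.

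**Working it through.** **1. The plan's own figures.** Inputs from section 11.0, Sample size considerations: expected proportion 0.80, half-width 0.05, two-sided 95% normal approximation, dropout 20%.

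- n = 1.96² x 0.80 x 0.20 / 0.05² = 245.85, rounded up to 246.
- 246 / (1 - 0.20) = 307.5, rounded up to 308. Planned enrolment is 310.

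These figures reproduce and are not in dispute.

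**2. Shifts open to each baseline level under Table 1.**

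| Baseline | Improving shifts | 'No change' | 'Worsening' |
|---|---|---|---|
| I | 0 | 1 (I to I) | 4 |
| II | 1 | 0 | 4 (including II to II) |
| III | 2 | 1 | 2 |
| IV | 3 | 1 | 1 |
| V | 4 | 1 | 0 |

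Level I is the only starting level with no improving shift. II to II is not listed under 'No change', so it falls into 'Worsening'. That is a separate slip and does not alter a Moderate-or-better proportion.

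**3. If response means Moderate or better.** Let f be the share of the denominator at baseline Level I and r the response rate in Levels II-V. Level I contributes no responders, so:

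overall rate = (1 - f) x r, which cannot exceed 1 - f.

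The protocol does not give f or r. For illustration, take r = 80% and 246 evaluable patients:

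| Assumed f | Level I patients (246 x f) | Overall rate | Ceiling | r needed for 80% overall |
|---|---|---|---|---|
| 0% | 0 | 80% | 100% | 80.0% |
| 5% | about 12 | 0.95 x 80% = 76% | 95% | 0.80/0.95 = 84.2% |
| 10% | about 25 | 0.90 x 80% = 72% | 90% | 0.80/0.90 = 88.9% |

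**4. If 'No change' also counted.** Let s be the share of Level I patients who stay at Level I. The overall rate becomes (1 - f) x r + f x s. With r held at 80% and s = 100%, f = 10% gives 0.90 x 80% + 0.10 x 100% = 82%. Level I patients then raise the rate whenever s exceeds r.

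**5. Precision if Level I is left out.** Half-width = 1.96 x √(0.80 x 0.20 / (246 x (1 - f))).

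- f = 0%: 5.00 points.
- f = 5%: 5.13 points.
- f = 10% (about 221 patients): 5.27 points.

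**The case against.** **The size is unknown and may be negligible.** Eligible patients have vertigo for which a physician chose the maximal recommended daily dose, which makes an absent or very mild baseline less likely. Exclusion criterion 1 also lets the investigator leave out unsuitable patients. This stands: nothing in the protocol supports a particular f, and if f is near zero the effect disappears.

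**The direction is not fixed.** A reader might infer that the design lowers the response rate by construction. That needs response to mean Moderate or better, which is the natural reading but is not written down. This stands.

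**The planning figure is not contradicted.** A reader might infer that the assumed 80% is too high. Section 11.0 states it for the whole study sample, so it can already include any Level I patients. The 80% in Levels II-V used above is an illustration. The cited global ratings total 86.2% and 89.1%. If Levels II-V responded at those rates, the overall rate would stay at 80% or more until f reached 1 - 0.80/0.862 = 7.2% or 1 - 0.80/0.891 = 10.2%.

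**No decision hangs on the result.** The program is single-arm and descriptive, with no success threshold on the primary endpoint. Under the Moderate-or-better reading the effect would understate effectiveness. This stands and limits the seriousness. The 5.0-point half-width is a precision target and should not be used as a tolerance for bias.

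**Broad entry is deliberate.** The program is pragmatic and non-interventional, and the protocol separates prescribing from inclusion. A reader might infer that a severity floor is needed at entry; the documents do not support that. Selecting on higher baseline scores in an uncontrolled before-after study of a fluctuating condition also invites regression to the mean. This stands against replacing the whole-population figure.

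**The matter is partly visible already, or could go in the SAP.** Secondary endpoint 1 tabulates severity levels at baseline and end of treatment, but only in patients completing treatment within 60 days, and as levels at each time point. It does not show how Level I patients enter the primary proportion. The entry criteria, endpoint population, response table and analysis set are all fixed in the protocol.

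**Conclusion.** The point holds as a mismatch between entry, denominator and response table, joined to a missing responder definition. Level I patients are eligible, are counted in the primary denominator and have no improving shift.

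Under Moderate or better, they cap the rate at 1-f and reduce it by f x r: 4 points at f = 5% and 8 points at f = 10%, with r assumed at 80%. If 'No change' counted, they could raise it instead. Both f and r are assumptions, and f may be small.

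The documents do not show that the reported rate will be materially low, that the 80% planning figure is wrong, or that the entry criteria are at fault. The sample size arithmetic is correct. The change is still worth making, because the issue falls on the sole primary endpoint and the data to resolve it are already collected.

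**What to change.** In section 6.3 and the primary analysis in section 11.0:

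1. Define clinical response as Moderate, Good, Very good or Excellent in Table 1.
2. Report the primary proportion with its 95% confidence interval in patients at baseline Levels II-V, beside the whole-population figure.
3. Tabulate baseline Level I patients separately as remained at Level I or worsened, with their number.

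Leave sections 7.1.1 and 7.1.2 unchanged.

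The cost is a few sentences and no new data, since the score is already taken at Visit 1. The restricted set gives a slightly wider interval, about 5.3 against 5.0 points at f = 10%. It also selects on higher baseline scores and so is more open to regression to the mean, which is why both figures should be shown.
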